### Statistical analysis

2.8

As we have 3 co-primary hypotheses, each co-primary hypothesis will be considered statistically significant if a two-sided p < 0.0167 (Bonferroni-corrected) is obtained. For the analysis of the coprimary outcomes, LLM will be employed, using a first order regressive covariance structure, which includes all observed variables without the need of imputing missing data. The dependent variable is score change on the HDRS-17. Independent variables are time (all observations until week 6), and group (‘double-active,’ ‘ptES-only’ and ‘double-sham’). We will test the statistical significance between the pairwise comparisons per our primary hypotheses. We will employ an intention-to-treat (ITT) approach.

For the analysis of the secondary outcomes, linear mixed-effects models will be employed analogically to the analysis for the primary outcomes. Binary outcomes (response and remission) will be modeled using mixed logistic regression at each timepoint. Improvement in other depressive domains will be evaluated using the same linear hierarchical models described.

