### Sample size calculation

2.7

For Psylect, we estimated a total sample size (n) of 210 randomized patients (70 patients per arm), to achieve the ability to observe statistically significant effects, with a power of 80% (1 − β = 0.8). Dropouts were assumed to increase monotonically (Weibull) and to be equally distributed between arms. We will use 4 measurements (continuous linear change from baseline, weeks 2, 4 and endpoint), between the 3 arms (time × group interaction), in the framework of linear mixed-effects models (LMM) [51,52].

For our sample size calculations, we assumed baseline depression scores and standard deviation (SD) of 25 (±5) on the HDRS-17, distributed equally between groups, based on previous works from our group [31,32,53]. Furthermore, we considered that: (1) placebo effects in the double-sham arm will impact baseline depression scores equal to 1 effect size (ES) in SD units (ES = difference in mean change divided by SD); (2) the ‘ptES-only’ arm will have the same placebo effects present in the double-sham arm (ES = 1), plus a treatment response of ES = 0.4; and, (3) the ‘double-active’ arm will have placebo effects (ES = 1) plus a larger response of ES = 0.8. Therefore, probable endpoint scores of 20, 18 and 16 were used, for ‘double-sham,’ ‘ptES-only’ and ‘double-active,’ respectively. The effect sizes were also chosen based on the results from our previous trials and considering that tDCS and online behavioral therapies have small to moderate effect sizes.

Sample size per arm was calculated based on the smallest detectable group difference (ES tDCS vs. combination = −0.4, ES placebo vs. tDCS = −0.4). Significance levels were Bonferroni corrected for 3-way pairwise comparisons (α = 0.05/3) to control family-wise error rate, while still allowing for more anti-conservative adjustment in the final analysis [54–56].

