**Figure 2 F2:**
[figure not shown]
Flow™ device designed for home use. The figure on the left shows the device and supporting iBT app. The figure on the right shows a simulation model of the electrode placement and corresponding electric field distribution on the cortex. The anode and cathode are placed over the left and right prefrontal cortices, respectively. The correct position, in terms of angulation and distance to the eyebrows, is achieved using the app<apos;>s augmented reality feature and the smartphone<apos;>s front camera.

**Table 1 T1:** Clinical scales and questionnaires used during PSYLECT.

	Baseline	W1	W2	W3	W4	W5	W6
Sociodemographic data/head measurements	✓						
Edinburgh Handedness Inventory (short version)	✓						
DDD	✓						
HDRS-17	✓		✓	✓	✓		✓
HAM-A	✓			✓			✓
MADRS	✓		✓	✓	✓		✓
CGI	✓			✓			✓
YMRS	✓		✓	✓	✓		✓
Blinding assessment - evaluator							✓
Blinding assessment - patient							✓
PANAS	✓			✓			✓
STAI-T	✓			✓			✓
STAI-S	✓			✓			✓
BDI - II	✓			✓			✓
Likert usability scale		✓	✓	✓	✓	✓	✓
tDCS side effect questionnaire		✓	✓	✓	✓	✓	✓

Abbreviations: DDD: Defined Daily Dose; HDRS-17: Hamilton Depression Rating Scale, 17-item version; HAM-A: Hamilton Anxiety Rating Scale; MADRS: Montgomery-Åsberg Depression Rating Scale; CGI: Clinical Global Impression; YMRS: Young Mania Rating Scale; PANAS: Positive and Negative Affect Rating Scale; STAI-T/STAI: State-Trait Anxiety Inventory; BDI-II: Beck Depression Inventory – II; tDCS: transcranial direct current stimulation.

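### An autoregressive, apparently equal-variance covariance on HDRS-17 change scores can understate the week-6 standard error, and sections 2.1, 2.7 and 2.8 do not agree on which effect is tested

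*Protocol article*

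**What the plan says.** Section 2.8 of the protocol article describes the primary analysis in a few sentences. For the co-primary outcomes, "LLM will be employed, using a first order regressive covariance structure". I read the model as the linear mixed-effects model (LMM) of section 2.7 and the structure as first-order autoregressive. The response is then named: "The dependent variable is score change on the HDRS-17". The terms follow: "Independent variables are time (all observations until week 6), and group". No interaction is named, and time is not said to be linear or categorical. Pairwise comparisons are to follow the primary hypotheses, and "each co-primary hypothesis will be considered statistically significant if a two-sided p < 0.0167 (Bonferroni-corrected) is obtained".

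Three other places bear on the same test:

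- Section 2.1 words all three co-primary hypotheses as differences in HDRS-17 change from baseline to endpoint.
- Section 2.7 plans differently: "We will use 4 measurements (continuous linear change from baseline, weeks 2, 4 and endpoint), between the 3 arms (time × group interaction". It applies a Bonferroni level of 0.05/3 "to control family-wise error rate, while still allowing for more anti-conservative adjustment in the final analysis".
- Table 1 schedules the HDRS-17 at baseline and weeks 2, 3, 4 and 6. Section 2.7 does not use week 3.

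**The concern.** All change scores of one patient share the same baseline value. If the correlation between baseline and a later visit falls with time, the variance of the change rises with time. A first-order autoregressive structure with a single variance cannot represent that. It pools the smaller early variances with the larger week-6 variance, so the week-6 comparison gets too small a standard error. The Bonferroni threshold then no longer holds the family-wise error at 5% for the three confirmatory tests. Secondary scales are to be modelled in the same way and inherit the problem.

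The second issue needs no assumption about correlation. An endpoint difference, a linear slope difference and a group main effect averaged over visits are different quantities. If the article names more than one, the choice of primary test stays open until someone fits the model.

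**Working it through.** **The plan's own figure.** 0.05/3 = 0.0167, as stated. With three pairwise tests among three equal arms, a correctly specified model has a family-wise error of 0.044, slightly under 0.05 because the tests are correlated.

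**Inputs.** From the article: SD 5 (baseline), 70 per arm, smallest difference 0.4 SD = 2 points (section 2.7); two-sided 0.0167 (section 2.8); visits at weeks 2, 3, 4 and 6 (Table 1). Assumed, because the article gives neither: the within-patient correlation and the SD after baseline.

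**Change-score variance.** With the same SD at every visit, Var(change at t) = 2 × SD² × (1 − ρ_t), where ρ_t is the correlation between baseline and week t. Take SD 5 and autoregressive raw scores with a two-week correlation of 0.8, so ρ_t = 0.8^(t/2):

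- week 2: 50 × (1 − 0.800) = 10.0
- week 3: 50 × (1 − 0.716) = 14.2
- week 4: 50 × (1 − 0.640) = 18.0
- week 6: 50 × (1 − 0.512) = 24.4

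The best-fitting equal-variance AR(1) has a common variance of 16.9. Model SE / true SE at week 6 = √(16.9/24.4) = 0.83. The critical value 2.394 therefore acts like 2.394 × 0.83 = 1.99, or about 0.046 per test instead of 0.0167. Simulation of null trials (70 per arm) gave 0.044 per test. Over two-week correlations of 0.7 to 0.9 the standard error is understated by 15 to 18%.

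**Family-wise error, change score as response, equal-variance AR(1), categorical visits, week-6 contrasts:**

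| Assumed truth | Family-wise error |
|---|---|
| SD 5, constant correlation | 0.044 (simulated 0.038–0.042) |
| SD 5, autoregressive (two-week 0.9) plus 20–30% measurement error | 0.066–0.076 |
| SD 5, autoregressive mixed with constant correlation | 0.075 |
| SD 5, purely autoregressive, two-week 0.7 / 0.8 / 0.9 | 0.104–0.123 large-sample; 0.096 / 0.107 / 0.122 simulated |
| SD rising from 5 to 7, autoregressive (weekly 0.87) | 0.131 simulated |

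With an unstructured covariance, the simulated family-wise error was between 0.035 and 0.050 in every scenario run, including those with 15% assumed dropout.

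**Other readings of the same model:**

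- Raw score as response, baseline as one of the measurements, purely autoregressive truth: 0.044–0.045 for the baseline-to-week-6 contrast, with or without week 3.
- AR(1) with visit-specific variances on change scores: 0.036–0.059 at week 6.
- Group main effect on change scores: 0.042–0.086. Linear slope on change scores, SD 5: 0.006–0.094.
- Unequal spacing alone, with equal variances: 0.044 at week 6, 0.071 for a slope.

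**Which effect is estimated.** Suppose the effect grows linearly to 2 points at week 6. The endpoint contrast is 2. A group main effect, weighting the four visits equally, is 2 × (2 + 3 + 4 + 6)/(4 × 6) = 1.25.

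Now suppose it grows linearly to 2 at week 3 and then holds: 1.33, 2, 2, 2 at weeks 2, 3, 4, 6. The least-squares slope on these post-baseline changes is 1.1667/8.75 per week, or 0.8 over six weeks. On the section 2.7 grid (weeks 0, 2, 4, 6; effects 0, 1.33, 2, 2) it is [(−1)(1.33) + (1)(2) + (3)(2)]/20 = 0.333 per week, or 2.0 over six weeks. One trajectory thus gives 0.8 or 2.0 depending on how the slope model is set up.

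**The case against.** The strongest objection is that section 2.7 counts baseline among the four measurements. Change is zero for everyone at baseline, so that model suggests the raw score is the response and change is the time-by-group effect. If the raw scores are autoregressive, the stated covariance is then right and nothing is inflated. This stands as an alternative reading. It does not remove the point, because section 2.8 names score change as the response.

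The article also never says equal variance, and a heterogeneous AR(1) is still first-order autoregressive. That stands too. Equal variance is the usual meaning of the unqualified term, but the analysis plan, which is not shown, could settle it.

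Three stronger readings are tempting and should not be drawn:

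- A reader might infer that the plan's family-wise error is 0.10 to 0.12. That needs the literal change-score response, equal variances, a week-6 contrast and purely autoregressive raw scores; the article does not supply the last of these at all.
- A reader might infer that no week-6 target exists. Section 2.1 states baseline to endpoint, and section 2.8 refers its pairwise tests back to the hypotheses. What is missing is agreement between sections on the model term.
- A reader might blame the uneven visits. Spacing adds almost nothing to the week-6 contrast and matters mainly for a slope test.

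An article may leave visit coding and degrees of freedom to the analysis plan, and their absence is not criticised here. The point rests on what the article does state.

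**Conclusion.** The point holds in conditional form. The covariance and response as worded in section 2.8 can understate the week-6 standard error. Under assumed inputs the family-wise error runs from about 0.04 (constant SD and correlation), through about 0.07 (measurement error added), to about 0.10–0.12 (purely autoregressive raw scores, SD 5), and somewhat higher if the SD grows, against a target of 0.05. No single value can be claimed, because the article gives neither the correlation nor the follow-up SD. The inflation largely goes away with the raw score as response or with visit-specific variances. Other contrasts behave differently, and some are conservative.

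The disagreement between sections 2.1, 2.7 and 2.8 on the tested term stands without any covariance assumption. It changes the quantity estimated, for example 1.25 instead of 2 points.

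**What to change.** State one primary model before treatment-coded outcomes are analysed: visit as categorical (weeks 2, 3, 4, 6), group, group by visit, and baseline HDRS-17 as a covariate, with an unstructured covariance. Name a fallback for non-convergence, such as heterogeneous variances or robust standard errors. Name the three pairwise group contrasts at week 6 as the co-primary tests, each at 0.0167, and bring sections 2.1, 2.7 and 2.8 into line with them. With baseline as a covariate, it no longer matters for these contrasts whether the response is the change or the score. Kenward-Roger degrees of freedom and a baseline-by-visit term are optional.

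The cost is wording, plus 10 covariance parameters (4 × 5/2) instead of 2, which about 200 patients estimate easily.

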**Methods:**

We will evaluate the efficacy, safety, tolerability and usability of (1) active ptES + active iBT (‘double-active’), (2) active ptES + sham iBT (‘ptES-only’), and (3) sham ptES + sham iBT (‘double-sham’), in adults with MDD, with a Hamilton Depression Rating Scale – 17 item version (HDRS-17) score ≥ 17 at baseline, during 6 weeks. Antidepressants are allowed in stable doses during the trial.

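### The stated primary model does not adjust for baseline HDRS-17, so it is valid but probably less precise than the data already collected would allow

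*Protocol article*

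**What the plan says.** Section 2.8 (Statistical analysis) describes a linear mixed model with a first-order regressive, presumably autoregressive, covariance. It fixes the outcome, "The dependent variable is score change on the HDRS-17", and the predictors, "Independent variables are time (all observations until week 6), and group". Significance is set so that "each co-primary hypothesis will be considered statistically significant if a two-sided p < 0.0167 (Bonferroni-corrected) is obtained". Continuous secondary outcomes are to be analysed in the same way.

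Section 2.7 (Sample size calculation) describes the model differently: four measurements, with baseline as one of them alongside weeks 2, 4 and the endpoint, compared through a time-by-group interaction. On inputs it says "we assumed baseline depression scores and standard deviation (SD) of 25 (±5) on the HDRS-17" and "probable endpoint scores of 20, 18 and 16 were used", so neighbouring arms differ by 2 points, or 0.4 SD. It gives no endpoint SD, no correlation between visits and no dropout rate.

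Table 1 schedules HDRS-17 at baseline. Section 2.2 requires a score of at least 17 for entry. Section 2.4 (Procedures) describes 1:1:1 computer randomization and mentions no stratification by severity.

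**The concern.** A change score subtracts the whole of the baseline value, whereas the data support subtracting only the part that predicts the endpoint. When the correlation is below 1 and the SDs are similar, the change score over-corrects. The arm that starts higher by chance then tends to show the larger fall, whatever the treatment does. Entering baseline as a covariate removes this and, apart from a degree of freedom, is never less precise.

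Precision matters here because each of three comparisons is tested at 0.0167 and two of them target only 0.4 SD. The covariate is already in hand, since no change score can be computed without it.

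**Working it through.** **Inputs.** Difference 2 points, baseline SD 5 and n = 70 per arm (section 2.7); two-sided alpha 0.05/3, critical value 2.394 (section 2.8). Assumed because not stated: baseline-endpoint correlation ρ from 0.3 to 0.7, endpoint SD equal to baseline SD, no dropout.

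**The plan's own figure.** A plain two-sample comparison with SD 5 needs 131 per arm for 80% power; 70 per arm gives 48.9%. The plan's method is a repeated-measures model, so this is not a refutation. For a linear time-by-group contrast at weeks 0, 2, 4 and 6 without baseline constraint, compound symmetry with correlation 0.7 gives 71 per arm, and first-order autoregression with adjacent correlation 0.8 gives 128. Without the correlations and the dropout rate, 70 can be neither confirmed nor refuted.

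**Gain from adjustment, single endpoint, equal SDs.**

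- Var(change) = 2·SD²·(1 − ρ)
- Var(adjusted) = SD²·(1 − ρ²)
- Ratio adjusted/change = (1 + ρ)/2, so the reduction is (1 − ρ)/2
- Power = Φ(2 / (SD\*·√(2/70)) − 2.394), where SD\* is the SD of the change score or of the adjusted score

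| ρ | SD\* change | SD\* adjusted | Variance reduction | Power at 70, change | Power at 70, adjusted | n per arm for 80%, change vs adjusted |
|---|---|---|---|---|---|---|
| 0.3 | 5.92 | 4.77 | 35% | 34.7% | 53.5% | 184 vs 120 |
| 0.5 | 5.00 | 4.33 | 25% | 48.9% | 63.3% | 131 vs 99 |
| 0.7 | 3.87 | 3.57 | 15% | 74.6% | 82.1% | 79 vs 67 |

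**If the endpoint SD is k times the baseline SD.** Var(change) = SD²·(1 + k² − 2ρk) and Var(adjusted) = SD²·k²·(1 − ρ²).

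| k | ρ = 0.3 | ρ = 0.5 | ρ = 0.7 |
|---|---|---|---|
| 1.0 | 35% | 25% | 15% |
| 1.2 | 24% | 13% | 3% |
| 1.4 | 16% | 6% | 0% |

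The entry threshold of 17 trims the baseline distribution, so k above 1 is plausible.

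**Four visits, unconstrained versus common baseline mean.** Under first-order autoregression the reduction in required n is 44–47% at adjacent correlation 0.5, about 33% at 0.7 and 24% at 0.8. Power at 70 per arm for the linear contrast goes from 50% to 64% at adjacent correlation 0.8. Under compound symmetry with correlation 0.7 it goes from 80% to 86%.

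**Chance imbalance.** The standard error of a baseline difference between two arms is 5·√(2/70) = 0.85 points. Given an observed difference D, the change contrast shifts by (1 − ρ)·D. For D = 0.85 that is 0.59, 0.42 or 0.25 points at ρ = 0.3, 0.5 or 0.7, against the 2-point target.

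**Does section 2.7 already supply the adjustment?** Only if arm means are held equal at baseline. With visits as categories, complete data and a free group difference at baseline, the time-by-group contrast is the difference in mean change, so nothing is gained. Neither section states the constraint, and the separate group term in section 2.8 points towards the unconstrained form.

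**The case against.** The best defence is that the predictor list in section 2.8 is condensed. It omits even the time-by-group interaction that section 2.7 names as the comparison, so a missing covariate need not be a decision to exclude one, and covariates are often left to an analysis plan. Section 2.7 also brings baseline into the model. This stands in part: the two sections leave open which model will be fitted. But section 2.8 does name the outcome, the covariance and the predictors, and neither section describes a form that would recover the baseline-adjusted precision.

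Two limits on the size also stand. The power table uses a single-endpoint formula, not the planned repeated-measures model. Under one assumed structure (compound symmetry, correlation 0.7), the unadjusted longitudinal contrast reaches about the planned 80% without help.

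A reader might infer that omitting baseline biases the result or invalidates the tests. It does not: averaged over randomizations the change-score contrast is unbiased and its type I error is valid. The shift from chance imbalance is the precision loss seen conditionally, not a second harm to be added to it.

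**Conclusion.** The point holds as a precision weakness in a valid analysis. Its size depends on two quantities the article does not give: a 35% to 15% variance reduction for ρ of 0.3 to 0.7 with equal SDs, 24% to 3% if the endpoint SD is 1.2 times baseline, close to nothing at 1.4 times with ρ of 0.7, and above 35% under autoregression with low correlation.

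A reader might take 15–35% as an established loss, or conclude that the trial is underpowered because of this omission. The document supports neither, because the correlation, the endpoint SD and the dropout rate are all unstated. The change is worth making because it costs nothing and adjustment is not expected to lose precision beyond a degree of freedom.

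**What to change.** Before outcomes are examined by arm, prespecify one of two forms:

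- keep HDRS-17 change as the outcome and add baseline HDRS-17 and its interaction with visit as fixed effects; or
- model the scores at all visits including baseline, with a common baseline mean across arms and treatment differences only after baseline.

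State the same form in sections 2.7 and 2.8, including the time-by-group term. Apply it to the continuous secondary outcomes, using each scale's own baseline value from Table 1.

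Adjusting for antidepressant use at baseline and for site is optional. The article says "Antidepressants are allowed in stable doses during the trial" and describes no stratification by either factor, and the gain has not been quantified.

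The cost is a few sentences of analysis wording and a few degrees of freedom. No new data, visits or patients are needed.

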## Discussion

3

PSYLECT will compare the efficacy, safety, tolerability, and usability of: (1) a combined and active regimen of ptES and iBT compared to active ptES in monotherapy; (2) a combined and active regimen of ptES and iBT compared to a double sham counterpart; and (3) active ptES in monotherapy versus a double sham, for the treatment of MDD, in adult patients, for 6 weeks. Antidepressant medications currently in use at baseline will be maintained throughout the trial, in stable doses.

After two RCTs developed by our team that have, respectively, studied the combination of tDCS and an antidepressant in a factorial design [32], and the non-inferiority of tDCS in comparison to an antidepressant [31], in PSYLECT we aim to evaluate the combination of a home-based tDCS protocol with an internet-based behavioral therapy approach.

Neurobehavioral strategies have been increasingly associated with tDCS for the treatment of MDD and other mental disorders, initially inspired by positive results with the combination of tES and motor rehabilitation for the treatment of stroke [19,20]. The neurobiological rationale behind these combinations is based on the ‘state dependency’ of targeted neural circuits [19], with recent evidence suggesting that ongoing neural activity is necessary for tDCS to bring forth neuroplastic effects, especially with concurrent interventions [20]. Previously, Segrave et al. studied the combination of tDCS with cognitive-control training (CCT) in 27 patients with MDD, and observed that the combined treatment demonstrated superior efficacy when compared to either treatment alone, in the reduction of MADRS scores, after 3 weeks [21]. Brunoni et al. (2014) [22] also studied the treatment effect of concurrent tDCS and CCT in 37 patients with MDD. In this study, although both arms (active CCT + active tDCS and active CCT + sham tDCS) displayed similar improvements, it was observed that among patients who received active tDCS, a greater reduction in depressive symptoms was observed in older individuals with better performance in speed and flexibility of information processing, possibly indicating greater engagement of the DLPFC [22]. Recently, another pilot study (n = 31) observed that the combination of tDCS and mindfulness-based cognitive therapy in depressed patients was superior in the maintenance of clinical improvement at a follow-up assessment, as compared to tDCS alone, strengthening the hypothesis that a combined approach could offer therapeutic advantages over tDCS in monotherapy [57].

Despite these advancements in tDCS research and methodology, patient access to the technique is still limited, mainly for logistical reasons. Daily tDCS sessions, performed over several weeks, in clinical or research facilities, can present a challenge to patients, especially in pandemic scenarios [58]. On the other hand, home-use tDCS devices have only recently been developed. Guidelines for conducting research with tDCS at home already exist [18], but few trials have investigated this procedure. An open-label pilot study (n = 34) [16] and a case series (n = 5) [17] have observed that home-use tDCS for MDD could be feasible, safe and tolerable.

In line with the rationale in the paragraph above, we understand that psychological interventions (i.e. neurocognitive interventions, such as psychoeducation or behavioral activation) performed in research facilities could also present similar logistical challenges. In this sense, it is noteworthy that these remote interventions have been used for depression in the last 30 years, according to the available technology in each period (for example, through books, phone calls, software, text messages and, more recently, through smartphone apps). Automated programs are usually carried out through interactive modules and multimedia techniques (photos, advice, sketches, and videos), to engage and motivate patients, generally in an add-on strategy to first-line treatments. Online interventions can be multifaceted, including cognitive training, self-monitoring of mood, mindfulness, psychoeducation, behavioral activation, and cognitive bias modification [59]. A positive trend was observed for fully automated applications and for interventions that provided user feedback (i.e. statistics and progress) [59].

However, one limitation of online psychological interventions [59] is the lack of a clinically verified MDD diagnosis in enrolled patients. This shortcoming was addressed by Josephine et al. (2017), who conducted a systematic review of CBT apps in the treatment of clinically diagnosed MDD [25]. Reviewing data from 19 selected studies, the authors still observed a statistically significant pooled effect size [Hedge<apos;>s g = −0.90, (95% CI: −1.07,−0.73; I2 = 0%)], favoring the active interventions over waiting lists [25]. However, only a small minority of online interventions are supported by controlled studies and many might profit from the ‘digital placebo effect,’ characterized as “placebo-like effects seen from mobile health interventions, such as smartphone apps, and which can influence the overall therapeutic response [60]. In PSYLECT, we use a sham app, instead of no intervention, in consonance with our endeavor to better quantify the digital placebo effect. Furthermore, hundreds of apps are currently available for the treatment of depression, but few studies have been carried out comparing the effect of these internet-based interventions versus sham, in real-life scenarios, and with larger and more heterogeneous clinical samples [61]. Moreover, only a small minority of commercially available mental health apps are supported by evidence from controlled studies [29].

Therefore, the PSYLECT trial builds from accumulated translational knowledge related to the neurobiological rationale of ‘target engagement’ [19], i.e. stimulating the same brain regions of interest with two diverse, but possibly synergistic, interventions: ptES and iBT.

